**Methods:**

We will evaluate the iSMEsH intervention regarding its effects on biased attitudes, knowledge, and self-efficacy among GPs. A sequential explanatory mixed-methods design (QUAN → qual) will be applied in three steps: (1) pre-implementation focus groups and a panel discussion with individuals with lived ED experience and GPs to design the intervention, (2) conduction of a randomized, wait-list controlled trial of the online training trial with GPs and medical students, and (3) post-implementation qualitative interviews with GPs. Quantitative data (step 2) will be analyzed using mixed-measures ANOVAs and contrast analyses (per-protocol) as well as corresponding 2 × 3 linear mixed models with fixed and random effects (intention-to-treat). Qualitative data from step 3 will be analyzed using thematic analysis as outlined by Braun and Clarke (2006). Ethical approval was granted by the Ruhr-University Bochum Ethics Committee (AZ 2023−1106). Participants will provide written or digital informed consent.

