### Objectives

This project aims to sensitize GPs in primary care in Germany to the occurrence and manifestation of EDs in men, to impart knowledge and specific skills, and to act against the stigmatization of EDs as “women’s diseases”. Towards that end, we will develop, disseminate, and evaluate an intervention (in terms of implementation and efficacy) adapted for Germany, based on an existing online training course, “Eating disorders in boys and men for doctors”. Although a preliminary version of the training course has already been created by our group and made openly available [19], it remains unclear who uses the course, whether it is accepted and implemented as intended, and how effective the course is as an intervention against stigmatization. Thus, the objectives of the current project are (1) to revise and optimize the existing training materials for their use in the German healthcare system, to (2) systematically record and evaluate aspects of implementation according to the “Implementation Outcomes” framework model [20] (i.e., acceptability, feasibility, appropriateness, adoption, fidelity, penetration, sustainability), and to (3) assess the effects of the intervention on reducing the identified sources of stigmatization (knowledge deficits, biased attitudes, low counselling and action competence). In this regard, we hypothesized that participation in the intervention will lead to individual increases in knowledge, decreases in stigmatizing attitudes, and increases in self-efficacy.

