### Participant timeline

Individuals interested in taking part in the study can self-enroll via a webform on the project website (https://maennermitessstoerung.rub.de), which is referenced as link and QR code in leaflets and mailings. At enrollment (-t_1_), participants will answer baseline and sociodemographic questions, undergo eligibility assessment and be allocated to their respective participant group (GP or medical student) and study arm (intervention or wait-list control). Participants allocated to the wait-list control groups will be informed that they need to wait 14 days for the online training. Participants of the wait-list control groups will be meanwhile invited to a quantitative pre-participation assessment at t_1_ within the two-week waiting period, after which they will receive the personalized login credentials for the online learning platform to administer a quantitative pre-intervention assessment at t_2_ (end of the waiting period), then followed by the actual online training and a quantitative post-intervention assessment at t_3_. By contrast, participants allocated to the intervention group directly receive personalized login credentials for the learning platform at t_1_ (enrollment) and administer pre-intervention assessments before participating in the online training, followed by a quantitative post-intervention assessment at t_2_. Intervention group participants will be contacted to administer a quantitative post-participation/follow-up assessment at t_3_ another 14 days after they have completed the online training. Both groups will have 14 days to complete the training. To minimize the risk of participant dropout, participants will receive reminder emails on several time points during their participation (a reminder for completing the pre-survey 1 week after receiving the pre-survey link, a reminder for completing the online training one week after receiving login credentials and another reminder two days before termination of the 14-days participation time window, and a reminder for the post-survey 1 week after receiving the post-survey link). This procedure applies to both GPs and medical students allocated to the respective study arms. Finally, selected participants of the GP groups are invited to a qualitative telephone interview (t_4_) about four months after completion of the online training and respective quantitative assessments (see Fig 2).

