### Sample size

To determine the appropriate sample size for the planned quantitative analysis (e.g., a 2x3 repeated measures ANOVA with a within-between interaction), an a priori power analysis was conducted using G*Power 3.1.9.7 software [30]. The aim was to achieve a power of.80 [31] with an alpha level of.05. A small-to-medium effect size (*f* = 0.15) as found in prior ED-related anti stigma research [15] and moderate correlation (*r* = .50) among the repeated measures were assumed, as observed in similar fields and due to practical significance considerations. The epsilon (ε) was set to 1, assuming sphericity, which is the most conservative scenario. Using these parameters, the G*Power analysis indicated that a total sample size of 74 participants is required, i.e., a minimum of 37 participants per group. Considering dropouts and cases with insufficient plausibility or quality of data, the study aims for an experimental group of approximately 50 GPs and a wait-list control group with further 50 GPs. To estimate the needs and benefits of future curricular use, the intervention will also be made accessible to approximately 50 medical students in their clinical training year. For the qualitative analyses, up to ten participants with lived experience of EDs and additional GPs for the pre-implementation focus group and panel discussion, and up to 50 GPs for the telephone-based qualitative post-implementation interviews were considered sufficient.

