### Data analysis

Qualitative data analyses will be conducted using MAXQDA [39] version 24.5.1. Quantitative data analyses will be performed using R [40] and SPSS [41].

Regarding quantitative data, we will conduct two sets of analyses. These will be per-protocol analyses and intention-to-treat analyses. For the per-protocol analyses, we will compute a 2 (intervention vs. wait-list control) x 3 (timepoint) mixed-measures ANOVA per each outcome and participant group, accounting for the two groups (intervention vs. wait-list control group) and the three time points of quantitative assessment. The intention-to-treat analyses will be conducted using a corresponding 2 x 3 mixed model, with by-participant random intercepts (and slopes, if justified by the data). We will also conduct contrast analysis for the 2 x 3 design (1 −1 −1 1 1–1) to directly test the predicted interaction pattern. The change from pre- to post-intervention will be estimated with a paired-samples t-test for any participant that completed the intervention. Quantitative implementation data will be aggregated descriptively and compared between groups.

The per-protocol analysis will use case-wise exclusions in case of missing data. In case of dropout/case exclusions, the ITT mixed model will be conducted with and without multiple imputation based on predictive mean matching functioning as a sensitivity analysis.

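### The contrast described as a direct interaction test is, in the written cell order, mostly a test of the t1-to-t3 change common to both arms

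*Protocol article*

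**What the plan says.** The Data analysis section sets out a "2 (intervention vs. wait-list control) x 3 (timepoint) mixed-measures ANOVA per each outcome and participant group" for the per-protocol set and a corresponding mixed model for intention-to-treat. It then adds a "contrast analysis for the 2 x 3 design (1 −1 −1 1 1–1) to directly test the predicted interaction pattern". The six cells are not labelled, and the last weight is read here as −1. The abstract places the contrast in the per-protocol set: "Quantitative data (step 2) will be analyzed using mixed-measures ANOVAs and contrast analyses (per-protocol".

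The Participant timeline section fixes what each cell means. The intervention arm trains first, "followed by a quantitative post-intervention assessment at t_2", and has a follow-up at t3. The wait-list arm has a "pre-intervention assessment at t_2_ (end of the waiting period"), then trains and is assessed again at t3. The hypothesis in the Objectives section is "increases in knowledge, decreases in stigmatizing attitudes, and increases in self-efficacy".

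**The concern.** A contrast tests only the group x time interaction if its weights sum to zero within each arm and at each time point. Otherwise it also picks up a main effect. The randomised information about efficacy lies in the interaction: at t2 one arm has been trained and the other has not. A change from t1 to t3 that both arms share has no untrained comparator, because both arms have been trained by t3. It could be training, retesting on the same items, or change over calendar time.

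If the planned weights load mainly on that shared change, a significant result could be reported as the predicted interaction, and so as a randomised effect, when it shows only that scores moved in both arms.

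**Working it through.** **Inputs.** The weights and factor order come from Data analysis and the cell meanings from Participant timeline. Sample size gives "The aim was to achieve a power of.80 [31] with an alpha level of.05", "A small-to-medium effect size (*f* = 0.15"), r = .50, sphericity, 37 per group required and about 50 GPs per arm targeted. Assumed, because the article does not state them: a two-sided contrast test, unit SD, and a shared t1-to-t3 drift d between 0 and 0.5 SD.

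**1. The plan's own figure.** For the within-between interaction with m = 3 measures, λ = f²·N·m/(1 − r) = 0.0225 × 74 × 3 / 0.5 = 9.99, with df = 2 and 144. Power is 0.806 at N = 74 and 0.795 at N = 72. The stated 74 is reproduced, so the sample size belongs to the group x time F test and not to the contrast.

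**2. What the weights contain (group-first order).**

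| | t1 | t2 | t3 | arm sum |
|---|---|---|---|---|
| Intervention | 1 | −1 | −1 | −1 |
| Wait-list | 1 | 1 | −1 | +1 |
| time sum | 2 | 0 | −2 | |

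Total squared weight is 6.
- Time: (2² + 0² + 2²)/2 = 4.00, or 67%.
- Arm: (1² + 1²)/3 = 0.67, or 11%.
- Interaction: 6 − 4.00 − 0.67 = 1.33, or 22%.

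Written out, the contrast equals [wait-list t2 − intervention t2] + [both arms at t1 − both arms at t3]. With a lasting training effect τ and no drift its expected size is τ + 2τ = 3τ. Only the first τ comes from the trained-versus-untrained comparison.

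**3. Behaviour when the training does nothing.** A shared drift d gives an expected value of 2d, whatever the level at t2, because the t2 weights cancel. Each arm's contrast score has variance (1 − r)·Σw² + r·(Σw)² = 0.5 × 3 + 0.5 × 1 = 2. So SE = √(2/n + 2/n), which is 0.283 at n = 50 and 0.329 at n = 37. A noncentral t with 2n − 2 df gives these rejection rates:

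| d (SD) | n = 50 per arm | n = 37 per arm |
|---|---|---|
| 0 | 5% | 5% |
| 0.1 | 11% | 9% |
| 0.2 | 29% | 23% |
| 0.3 | 56% | 44% |
| 0.5 | 94% | 85% |

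Simulation agrees: 28.6%, 55.1% and 94.0% at n = 50, and 22.5%, 44.4% and 85.5% at n = 37, for d = 0.2, 0.3 and 0.5.

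**4. A true interaction contrast.** For intervention (−1, 2, −1) and wait-list (1, −2, 1), every arm sum and time sum is zero, so a shared drift has expectation 0. Simulated rejection at n = 37 was 4.6% to 5.1% over the same range.

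**5. The other cell order.** Listed time-first, the weights would be intervention (1, −1, 1) and wait-list (−1, 1, −1): 0% time, 11% arm, 89% interaction. Shared drift would cancel and the rate would stay at 5%.

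**The case against.** The strongest objection is that the cells are unlabelled and every figure in the drift table depends on the group-first order. The time-first weights are also close in shape to the replacement in step 4. This stands to the extent that the group-first reading is an inference. It is still the better one. The design is written with group first. In that order the weights reproduce the predicted means cell by cell: the intervention arm moves at t2 and stays, and the wait-list arm moves only at t3. As a predicted profile, the time-first order would return the intervention arm to its starting level at t3, which the Objectives do not hypothesise. The resemblance to the replacement does not help, since those are weights with main effects removed, not predicted means. Under either order the arm sums are ±1, so neither is a pure interaction contrast.

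It can also be said that the t1-to-t3 change is not mere nuisance, because the hypothesis predicts it once both arms are trained. That is correct. The weights are a legitimate test of the overall predicted pattern; the fault is to call it a direct test of the interaction.

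Three stronger readings may tempt a reader, and the article does not support them:
- **That the trial's efficacy conclusion carries a 29% to 94% error rate.** The contrast is additional to the ANOVA and mixed model, nothing makes it decisive, and shared drift does not affect their group x time terms.
- **That a sizeable drift is to be expected.** Retesting on a ten-item knowledge test is a plausible source, but no size is given. The quizzes belong to the training modules, so gains from them are training effect, and the reminders only prompt completion.
- **That the 11% arm component causes false positives.** Under randomisation with no training effect, its expectation is zero.

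**Conclusion.** The point holds for the contrast and its label. In the written order, the test presented as direct evidence of the interaction gives 22% of its squared weight to the interaction and 67% to a change that the wait-list control cannot separate from retest or secular effects. Its false-positive rate is the nominal 5% with no shared drift. It rises to about 29%, 56% and 94% at 50 per arm (23%, 44% and 85% at 37 per arm) for drifts of 0.2, 0.3 and 0.5 SD. These rates rest on the group-first order, r = .50, a two-sided 5% test and drift sizes that are assumed. The planned group x time tests and the sample size of 74 are not called into question.

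**What to change.** Label the six cells. Replace the weights with the interaction part of the predicted pattern: intervention (−1, 2, −1) and wait-list (1, −2, 1), with signs reversed for stigma. Alternatively, test the between-arm difference at t2 adjusted for t1. If the present weights are kept, describe the result as a test of the overall predicted mean pattern that includes uncontrolled pre-post change, and do not report it as an interaction test or as randomised evidence of efficacy.

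The cost is a line of wording and code, with no new data. The p-value may be less favourable. With a true lasting effect of 0.3 SD, no drift and 37 per arm, the present weights reject in 77% of trials (3 × 0.3 / 0.329 = 2.7 SE) and the interaction weights in 31% (2 × 0.3 / 0.403 = 1.5 SE). Much of the lost power came from the pre-post change that has no control.

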To promote participant retention, participants will receive reminder emails (see section “Participant Timeline”) and a compensation for completing the survey and online intervention (i.e., monetary reimbursement for GPs, participation in the prize draw for online vouchers for medical students). Further, the survey is set up so that most questions cannot be skipped to proceed or submit the survey, with in-built reminders of unanswered items.

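### The stated missing-data sensitivity analysis compares two missing-at-random analyses, so their agreement says nothing about leavers who gain less

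*Protocol article*

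**What the plan says.** The Data analysis section plans two sets of quantitative analyses.

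- **Per-protocol:** a 2 × 3 ANOVA on complete cases. "The per-protocol analysis will use case-wise exclusions in case of missing data".
- **Intention-to-treat:** a 2 × 3 linear mixed model with a random intercept per participant, and random slopes where the data support them. If participants drop out or cases are excluded, "the ITT mixed model will be conducted with and without multiple imputation based on predictive mean matching functioning as a sensitivity analysis".

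The section names no missingness assumption and does not list the variables in the imputation model. No other analysis in the article is called a sensitivity analysis for missing data.

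Three other places bear on the point.

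- **Data collection methods:** "most questions cannot be skipped to proceed or submit the survey". Missing data will therefore be mainly whole assessments, not single items.
- **Sample size:** 74 participants are required and about 100 GPs are sought. The margin is explained by "Considering dropouts and cases with insufficient plausibility or quality of data".
- **Participant timeline, and Study setting and participant recruitment:** in the intervention arm the t2 survey follows the training and t3 is timed from its completion. GPs are paid once they finish. The wait-list t2 survey requires no training.

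**The concern.** A sensitivity analysis for missing data is useful when it changes the assumption that cannot be checked from the data. Here that assumption is that participants who leave would have scored like retained participants with the same observed values. The mixed model uses it through the likelihood. Predictive mean matching uses it by drawing donors from retained participants with similar predicted scores. Changing from one to the other changes the modelling route but leaves the assumption in place.

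The untested departure is plausible in this trial. Training is voluntary and self-paced, and intervention-arm follow-up is tied to finishing it. People who stop partway have seen less of the content, and may gain less than completers with the same t1 score. If so, the intention-to-treat effect is too large, and both runs carry the same error.

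**Working it through.** **1. The plan's sample size.** Inputs from the Sample size section: "A small-to-medium effect size (*f* = 0.15) as found in prior ED-related anti stigma research"; "moderate correlation (*r* = .50) among the repeated measures were assumed"; ε = 1, α = .05, power .80, m = 3 time points, k = 2 groups.

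λ = f²·N·m·ε/(1 − r) = 0.0225 × 74 × 3/0.5 = 9.99, with df₁ = (k − 1)(m − 1) = 2 and df₂ = (N − k)(m − 1) = 144. The noncentral F distribution gives power 0.806 at N = 74 and 0.795 at N = 72. So 74 is the smallest even N that reaches .80, and the plan's figure is reproduced. The margin from 100 to 74 is 1 − 74/100 = 26%.

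**2. The effect size on the SD scale.** In the contrast given in the Data analysis section the arms differ only at t2. For a t2 difference d, the interaction deviations are ±d/3 at t2 and ∓d/6 at t1 and t3. Their mean square is (d²/9 + d²/36 + d²/36)/3 = d²/18. Hence d = f × √18 = 0.15 × 4.243 = 0.636 SD.

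**3. Both runs when leavers gain less.** Settings: 50 per arm, 13 lost per arm at t2 (26%), r = .50, bivariate normal scores, 1,500 trials per row, imputation within arm (20 imputations, 5 donors) using the same variables as the likelihood analysis. If lost intervention participants gain δ less than retained ones, the true average effect is 0.636 − 0.26 × δ.

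| δ (SD) | Truth | Likelihood | With predictive mean matching |
|---|---|---|---|
| 0 | 0.636 | 0.634 | 0.635 |
| 0.20 | 0.584 | 0.637 | 0.638 |
| 0.40 | 0.532 | 0.643 | 0.643 |
| 0.636 | 0.471 | 0.643 | 0.643 |

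The bias in the last row is in effect the assumed input: 0.26 × 0.636 = 0.165, about 0.17 SD. What the simulation adds is that the two columns do not separate as the truth moves. Their correlation is .99, and the SD of their difference is 0.04.

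**4. A harder test.** Settings: N = 100, three waves, a random-intercept REML model with group-by-time effects, true t1-to-t2 arm difference 0, loss of 22–32% per arm, 500 trials per row. In the intervention arm the log-odds of loss rise by the stated slope per SD of smaller gain. The slopes are assumptions.

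| Slope | Mixed model (SD) | With predictive mean matching (SD) | Rejection, each run | Same decision |
|---|---|---|---|---|
| 0 | 0.002 | 0.002 | 6.6%, 6.0% | 97% |
| 1 | 0.181 | 0.171 | 13.0%, 12.4% | 97% |
| 2 | 0.316 | 0.305 | 28.0%, 27.6% | 92% |

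The mean absolute difference between the runs is 0.04–0.05 SD in every row, so its size gives almost no sign of the bias.

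**5. What auxiliary variables change.** Settings as in step 3, with one baseline auxiliary that is related to intervention-arm gain, drives intervention-arm loss, and is used only in the imputation. The strengths are assumptions.

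| Correlation with gain | Truth | Likelihood | Imputation with auxiliary | Bias, likelihood → imputation |
|---|---|---|---|---|
| .3 | 0.63 | 0.71 | 0.65 | 0.08 → 0.02 |
| .5 | 0.63 | 0.77 | 0.67 | 0.14 → 0.04 |
| .7 | 0.63 | 0.83 | 0.68 | 0.20 → 0.05 |

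The auxiliary removes 71–75% of the bias, and the runs visibly separate. They do so because the loss is explained by a measured variable, which is still missing at random given that variable.

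**The case against.** The strongest case against the point has five parts.

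- **The runs need not agree.** A reader might infer that the comparison passes by construction. The documents do not support that. The imputation model is not given, and the Outcomes and Data collection methods sections list many baseline variables that could enter it. Step 5 shows that a good auxiliary can expose part of the problem. This stands. It does not reach loss that depends only on unobserved outcomes.
- **The comparison has a use.** Knowledge is a score from 0 to 10 and self-efficacy a sum from 3 to 12, and the mixed model may have random intercepts only. Predictive mean matching relaxes the distributional form and need not impose that covariance structure. This stands, and is a reason to keep it. Steps 3 and 4 use normal scores with a common correlation, so they do not show this benefit.
- **No robustness claim is made.** A reader might infer that agreement will be reported as robustness to dropout. The text only calls the comparison a sensitivity analysis and does not say how agreement will be worded.
- **The 26% is not a dropout rate.** The margin also covers data-quality exclusions, and the target per arm is approximate. This stands, so the 0.17 SD is a scenario and not a forecast.
- **Detail may sit in an analysis plan that is not shown.** A departure analysis could be specified there. The point therefore rests on what the article fixes: it names a procedure and gives it a label, and that procedure does not vary the missingness assumption.

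The per-protocol ANOVA does not fill the gap. Complete-case analysis generally needs a stricter assumption than the mixed model, and it is not presented as a sensitivity analysis.

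**Conclusion.** The point holds in a limited form. The comparison that the article labels a sensitivity analysis stays within missing at random. With the same variables in both runs, the estimates nearly coincide; with auxiliaries they can differ. In neither case does agreement bear on whether leavers gained less for reasons not captured in the data.

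The illustrative size is about 0.17 SD of upward bias in both runs, against a planned effect of 0.636 SD. It assumes that 26% of the intervention arm is lost, that these participants gain nothing, that the wait-list group does not change between t1 and t2, and that the imputation uses the mixed model's variables only. The protocol gives no dropout rate or mechanism, so the bias sizes in all the simulations are conditional on assumed loss. That neither run varies the missingness assumption does not depend on those sizes.

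The sample size is unaffected. The change is worth making because loss tied to completing the training is plausible and the remedy is cheap.

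**What to change.** 1. Keep the mixed model as the missing-at-random analysis and say that this is its assumption.
2. Keep predictive mean matching, described as a check within missing at random. Name its auxiliaries from data already collected: baseline covariates, modules reached and module ratings. Impute within arm, since the wait-list group has no module data before t2.
3. Add a departure analysis. Impute missing intervention-arm scores, then lower the imputed gains by 25, 50, 75 and 100%, where 100% is the wait-list t1-to-t2 trajectory. Use that same trajectory as the floor for imputed t3 scores, because the wait-list group has had access to the training by t3. Report the shift at which the conclusion changes.

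In the step 3 scenario (26% lost, no wait-list change), the steps lower the average effect by 0.26 × 0.636 × (0.25, 0.50, 0.75, 1) = 0.041, 0.083, 0.124 and 0.165 SD, to 0.595, 0.553, 0.512 and 0.471 SD.

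The cost is a few lines of R and a sentence or two in the analysis section. Recruitment and data collection do not change. The downside is slightly more analysis work and possibly a less favourable robustness statement.
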